### 5.1.3 Potential confounders

We will consider adjusting for age, sex, socioeconomic position, geography and where possible, comorbidities. More specifically, we anticipate adjusting for the following confounders in Scotland: age (five-year bands^^[[3]](#footnote-2)^^), sex, socioeconomic position (SEP) measured by quintiles of the Scottish Index of Multiple Deprivation (SIMD) (1 refers to most deprived and 5 refers to least deprived), residential settlement measured by the urban/rural 6 fold classification (1 refers to large urban areas and 6 refers to small remote rural areas), household size, number and types of comorbidities commonly associated with COVID-19 illness (asthma, chronic kidney disease, liver cirrhosis, chronic neurological condition, heart failure, diabetes (type 1 and type 2), dementia, coronary heart disease), risk factors (smoking status, blood pressure, body mass index (BMI)) and Health Board.

In Brazil, we anticipate adjusting for age (five-year bands), sex, the primary reason for vaccination, race/ethnicity and calendar week will be accounted for within the statistical models.

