## 2.2 Objectives

By vaccine type, we seek to:

1. Estimate Odds Ratio (OR) against the composite outcome of COVID-19 hospitalisation/death of individuals with booster dose versus individuals without booster dose.
2. Estimate Odds Ratio (OR) against confirmed SARS-CoV-2 infection of individuals with booster dose versus individuals without booster dose.
3. Estimate Rate Ratio (RR) against the composite outcome of COVID-19 hospitalisation/death as a function of time post maximum effect of the booster dose of a COVID-19 vaccine.
4. Estimate RR against the separate outcomes of i) COVID-19 hospitalisation; ii) COVID-19 death as a function of time post maximum effect of the booster dose of a COVID-19 vaccine.
5. Assess if waning of protection from booster dose differs by age group, sex and being in a high-risk COVID-19 group

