# Data and Data Validation

## 4.1 Data variables available

Tables 1 and 2 lists the groupings of variables available for this study by data source. Exposure data are described in the vaccinations category. Outcome data are described in the secondary care, mortality and laboratory tests categories. The rest of categories contain data on potential confounding factors and effect modifiers.

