**Table 1: Data items/variables and data sources**

| **Data category** | **Data item** | **Data source** |
| --- | --- | --- |
| Demographic | Sex | GP |
|  | Age | GP |
| Socioeconomic | SIMD | GP |
| Other characteristics | Body Mass Index (BMI) | GP |
|  | Smoking | GP |
|  | Blood Pressure | GP |
| Geographic | Urban Rural Index (UR6); Health Board | GP |
| Clinical diagnoses | Underlying conditions  (e.g., asthma, cardiac disease, immunosuppression etc.) | GP |
| Vaccinations | Vaccine type | GP, TVMT |
|  | Vaccine dose | GP, TVMT |
|  | Vaccination date | GP, TVMT |
| Laboratory tests | RT-PCR positive SARS-CoV-2 | ECOSS |
|  | RT-PCR negative SARS-CoV-2 | ECOSS |
|  | Date of RT-PCR test | ECOSS |
| Genomic Vigilance | Date of prevalence of variants | GISAID |
| Secondary care | Hospital admissions | RAPID/SMR |
| Mortality | Death with COVID-19 as the main cause according to death certificate, or death within 28 days of a positive RT-PCR test for COVID-19 | NRS |
| Abbreviations: Scottish Index of Multiple Deprivation (SIMD), Body Mass Index (BMI), Electronic Communication of Surveillance in Scotland (ECOSS), Reverse-transcription polymerase chain reaction (RT-PCR); Turas Vaccination Management Tool (TVMT); Scottish Morbidity Record (SMR); National Records of Scotland (NRS) | | |

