### 5.1.4 Potential effect modifiers

Stratification into different population:

- Primary vaccination schedule (2 doses): ChAdOx1, BNT162b2
- Age group (18-49,50-64, 65+ years)
- Period of which variant (Delta or Omicron)
- Additional, given that VE may differ between those with multiple underlying medical conditions, that are related to serious COVID-19, we will stratify analyses by COVID-19 risk group when data allow. We will also consider stratifying analyses by vaccine type and calendar time (to reflect different dominant variants present in the country).

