### 5.1.5 Analytical techniques

We will commence analysis by conducting descriptive analyses to visually inspect trends in vaccination delivery, age-specific COVID-19 hospitalisations and COVID-19 deaths, including by age group and sex. This will include checking the number of people who have received two doses and the length of follow-up available following the second dose by vaccine type. Including plotting Lexis diagram to afford for the correlated structure of the data (Calendar Time/Length of Follow-up)

For the analysis consisting of individuals with at least two doses, we will stratify the cohort based on the month of the second dose of each individual. The vaccination status will be classified as:

- Second dose:
  - <2 weeks
  - 2-9 weeks
  - 10-19 weeks
  - ≥20 weeks without a booster dose [Reference Period]
- Booster dose:
  - <2 week
  - 2-4 weeks
  - 5-8 weeks
  - 9-12 weeks
  - ≥13 weeks

This variable will be used to fit a Poisson regression to obtain rate ratios (RRs) and their 95% confidence intervals (CIs). If we observe overdispersion, we will consider using Negative Binomial regression models or Poisson with robust standard errors. Models will be adjusted for the relevant confounders above, including a set of dummy variables for calendar week.

The models will be fit to a dataset with all events and a random sample, without replacement, of 100 individuals per event (for hospitalisation and death, 10 for positive tests). The sample weights will be calculated to represent the sampling fraction, thus ensuring the correct calculation of the person-years at risk for the whole population.

The primary analysis for the test negative will be on individuals who are symptomatic at the time of test and the date of symptom onset is 0-10 days before the test. We will then establish the number of weeks post-vaccination for the cases and controls calculated as time between sample collection date and vaccine dose. The odds' ratio will be calculated using a logistic regression. Adjusted for: race/ethnicity, comorbidities, dummy variables for calendar week, age (five-year bands), sex. Controls will be defined based on a negative test.

We will also construct a propensity score to be tested among those in the primary cohort and use this as an inverse propensity weight.

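### Immunosuppression is listed as available in the Scottish GP data but is missing, without a reason, from the comorbidity list that the Scottish cohort model adjusts for

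*SAP*

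**What the plan says.** Table 1 gives the GP record as the source of underlying conditions in Scotland and illustrates them with "e.g., asthma, cardiac disease, immunosuppression etc". Section 4.1 explains what the non-exposure, non-outcome categories are for: "The rest of categories contain data on potential confounding factors and effect modifiers".

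Section 5.1.3 introduces the Scottish adjustment set with "More specifically, we anticipate adjusting for the following confounders in Scotland". It includes the number and the types of comorbidities, and itemises them as "asthma, chronic kidney disease, liver cirrhosis, chronic neurological condition, heart failure, diabetes (type 1 and type 2), dementia, coronary heart disease".

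Section 5.1.5 then says of the cohort Poisson model: "Models will be adjusted for the relevant confounders above, including a set of dummy variables for calendar week". For the test-negative design (TND) it says: "Adjusted for: race/ethnicity, comorbidities, dummy variables for calendar week, age (five-year bands), sex", with no itemised conditions. The same section plans a propensity score for the primary cohort and lists no covariates for it.

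Objective 5 in section 2.2 is to "Assess if waning of protection from booster dose differs by age group, sex and being in a high-risk COVID-19 group", and section 5.1.4 adds that "we will stratify analyses by COVID-19 risk group when data allow". Neither place defines the group.

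**The concern.** Of the three examples in Table 1, asthma and cardiac disease (as heart failure and coronary heart disease) reach the list in section 5.1.3, and immunosuppression does not. Because the one bracket defines both the types and the number of comorbidities, an immunosuppressed person with none of the eight listed conditions would enter the Scottish cohort model as having no comorbidity. Section 3.5 does not exclude such people.

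Immunosuppression could plausibly affect both when a person is boosted and the risk of COVID-19 hospitalisation or death. The main contrast is between bands of time since booster. Within a given calendar week, time since booster is fixed by the booster date, so the band of 13 weeks or more compares people boosted earlier with people boosted later. The calendar-week terms do not remove a difference in composition between those groups. If the share of immunosuppressed people differs between bands, the RRs shift for a reason other than waning, and a large cohort does not reduce that shift.

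**Working it through.** **Text check.** The SAP states no figure on this point, so there is none to reproduce. Set side by side:

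| Place in SAP | Immunosuppression |
| --- | --- |
| Table 1, with 4.1 | Named; available from GP data; in a category of potential confounders and effect modifiers |
| 5.1.3, Scottish list | Absent from eight itemised conditions; the bracket is not marked as examples |
| 5.1.5, cohort Poisson model | Refers back to the confounders above |
| 5.1.5, TND model | Comorbidities, not itemised |
| 5.1.5, propensity score | Covariates not listed |
| 2.2 and 5.1.4, risk group | Not defined |

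No section restores the condition to the cohort model or says that it was left out on purpose.

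**Illustrative size.** For one omitted binary confounder, the crude bias factor on a rate ratio is

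B = [1 + p1(R − 1)] / [1 + p0(R − 1)],

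where p1 is the prevalence of immunosuppression in the band of interest, p0 its prevalence in the comparison band, and R its rate ratio for the outcome. All three are assumptions: prevalence 2% to 8%, R from 3 to 5.

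- 4% v 2%, R = 3: 1.08 / 1.04 = 1.04
- 6% v 2%, R = 5: 1.24 / 1.08 = 1.15
- 8% v 2%, R = 5: 1.32 / 1.08 = 1.22
- Equal prevalence, any R: 1.00
- 2% v 4%, R = 3: 1.04 / 1.08 = 0.96
- 2% v 6%, R = 5: 1.08 / 1.24 = 0.87
- 2% v 8%, R = 5: 1.08 / 1.32 = 0.82

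For a late band against an early band, B above 1 would mimic waning and B below 1 would mask it. The booster band against the reference of 20 weeks or more without a booster is a separate contrast. It has its own p1 and p0, and nothing in the SAP says that these match those between booster bands.

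**The case against.** The strongest reply is that section 5.1.3 is provisional: it speaks of considering and anticipating adjustment, so the bracket is closed in form but is not a locked commitment. That is fair. It is still the only specific list in the SAP, and the cohort model points to it.

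Second, the bias factor is crude. The plan stratifies by month of second dose and adjusts for calendar week, five-year age bands, deprivation, BMI, smoking and eight conditions. Any part of the link between immunosuppression and booster timing that runs through these is already controlled. This stands, and the range above is not an estimate of residual bias. The listed covariates do not, however, identify an immunosuppressed person who has none of the listed conditions.

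Third, section 5.1.8 will consider negative-control outcomes if data allow. These could flag residual confounding but would not correct it, and they are not committed.

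A reader might infer three stronger points, and the SAP supports none of them:

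- That the booster RRs and the waning trend are confounded. The SAP gives neither the prevalence of immunosuppression by band nor its outcome risk, so neither size nor direction is shown. Quoting only the scenarios above 1, as 4% to 22% of false waning, would report half of the range.
- That the TND model also omits the condition. Its comorbidity term is undefined and does not refer to section 5.1.3; the open description in Table 1 could equally define it.
- That Objective 5 would count immunosuppressed people as low risk. The high-risk group is undefined, so it cannot be said to exclude them.

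**Conclusion.** The gap is real and narrow. In the Scottish cohort analysis, a condition that the SAP itself lists as available and as a potential confounder is missing from the itemised comorbidity adjustment, with no reason given. Residual confounding of the booster RRs and the waning trend therefore cannot be ruled out. On the assumed inputs the crude bias factor lies between about 0.82 and 1.22. It is 1.00 if prevalence does not differ between the bands compared, and should be nearer 1 to the extent that the planned adjustments capture the imbalance. The direction is unknown, and either direction is a reason to adjust. For the TND and for Objective 5 the defect is a missing definition, not a shown exclusion. The point does not extend to Brazil. It should be corrected before analysis, as an inexpensive improvement and not as a demonstrated bias.

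**What to change.** In section 5.1.3, add immunosuppression, taken from the GP record named in Table 1, to the Scottish comorbidity list, both as its own indicator and in the comorbidity count. If it is deliberately left out, give the reason.

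In section 5.1.5, include it among the covariates of the propensity score for the Scottish cohort, and state that the comorbidity term in the Scottish TND model includes it. In section 5.1.4, define the COVID-19 high-risk group used for Objective 5 and state that it includes immunosuppression.

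The cost is a line or two of SAP text and one indicator from data that the plan already lists. No stated figure in the SAP changes, and there is no material downside.

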## 3.4 Data sources

In Scotland, we will draw on the following databases:

- Primary care data: General Practices (n=940) for information on demographics, other population characteristics and vaccination data.
- Vaccination data: Vaccines administered in national vaccination centres and data available via the Turas Vaccination Management Tool (TVMT).
- Secondary care data: Hospital admissions through the Scottish Morbidity Record (SMR) and Rapid Preliminary Inpatient Data (RAPID).
- Laboratory test data: RT-PCR laboratory confirmed SARS-CoV-2 infection and data available via the Electronic Communication of Surveillance in Scotland (ECOSS) database.
- Mortality data from National Records Scotland (NRS)

Equivalent datasets will be used for other UK/international countries. In Brazil, we will analyse deterministically linked data provided by the Ministry of Health:

- COVID-19 vaccination (SI-PNI): Dates and types of vaccination administered, primary reason for vaccination, indigenous status, pregnancy status.
- Acute Respiratory Infection Suspected Cases (eSUS-Notifica): register of suspected and confirmed COVID-19 cases
- Severe Acute Respiratory Infection/Illness (SIVEP-Gripe): contains all hospitalisations and deaths due to severe acute respiratory illnesses, including COVID-19.

The above three databases all have whole population coverage, with returns from both public and private healthcare systems. However, data quality may vary geographically (typically data quality is better in the south of Brazil). Testing capacity has also improved over the course of the pandemic, but most improvements occurred prior to the vaccination programmes starting. In addition to the above datasets, it may be possible in the future to obtain linkage to general hospital records for patients treated within the public healthcare system (covering approximately 70% of hospitalisations in Brazil).

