## 3.5 Inclusion/exclusion criteria

Inclusion criteria for the primary cohort:

- Receive at least two doses of BNT162b2 or ChAdOx1 before or during the study period.

Exclusion criteria for the primary cohort:

- Inconsistent vaccination records (i.e. received a second dose with no record of a first dose, received doses from different vaccine types or interval between doses of less than 14 days)
- Missing essential covariates (sex, age, geography)
- Children (under the age of 18 years)
- Hospitalization previous to the study start date
- A positive test within 28 days of the study start date

Inclusion criteria for the TND:

- Receive at least two doses of BNT162b2 or ChAdOx1 at the sample collection date.

Exclusion criteria for the TND:

- Tests within 90 days of a previous positive test
- Negative tests followed by a positive test within 7 days
- Negative tests within 14 days of a previous negative test
- Missing essential covariates (sex, age, geography)
- Children (under the age of 18 years)

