**Table 2: Data items/variables and data sources in Brazil**

| **Data category** | **Data item** | **Data source** |
| --- | --- | --- |
| Sociodemographic | Sex | SI-PNI |
|  | Age | SI-PNI |
|  | Municipality-level IBP | SI-PNI |
|  | Education | (SIVEP-Gripe) |
|  | Race | SI-PNI, eSUS, SIVEP-Gripe |
|  | City |  |
| Clinical diagnoses | Underlying conditions  (Cardiac disease, chronic kidney disease, etc) | eSUS, SIVEP-Gripe |
| Vaccinations | Vaccine type | SI-PNI |
|  | Vaccine dose | SI-PNI |
|  | Vaccination date | SI-PNI |
|  | The primary reason for vaccination: 2 categories (comorbidities/other) | SI-PNI |
| Genomic Vigilance | Date of prevalence of variants | GISAID |
| Laboratory tests | Date of RT-PCR/rapid antigen test | eSUS |
|  | RT-PCR/rapid antigen positive SARS-CoV-2 | eSUS |
|  | RT-PCR/rapid antigen negative SARS-CoV-2 | eSUS |
| Secondary care  Mortality | COVID-19 hospital admission date | SIVEP-Gripe |
|  | COVID-19 death | SIVEP-Gripe/eSUS |
|  | COVID-19 death date | SIVEP-Gripe/eSUS |

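### The itemised Brazilian adjustment list and the shared test-negative list omit geography and deprivation, leaving the RR, the OR and the waning trend open to regional confounding of unknown size and direction

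*SAP*

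**What the plan says.** Section 5.1.3 opens with a general statement for both countries: "We will consider adjusting for age, sex, socioeconomic position, geography and where possible, comorbidities". It then itemises by country. The Scottish list includes "socioeconomic position (SEP) measured by quintiles of the Scottish Index of Multiple Deprivation (SIMD"), "residential settlement measured by the urban/rural 6 fold classification" and Health Board. The Brazilian list is shorter: "In Brazil, we anticipate adjusting for age (five-year bands), sex, the primary reason for vaccination, race/ethnicity and calendar week will be accounted for". It has no geographic term and no deprivation measure.

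Section 5.1.5 refers the cohort Poisson models back to the confounders of 5.1.3, plus calendar-week dummies. For the TND it gives one list with no distinction by country: "Adjusted for: race/ethnicity, comorbidities, dummy variables for calendar week, age (five-year bands), sex". Section 3.3 applies the TND in both countries.

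Section 3.5 excludes records from the cohort and from the TND for "Missing essential covariates (sex, age, geography").

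Table 1 lists SIMD, the urban/rural index (UR6) and Health Board for Scotland. Table 2 lists City (its source cell is blank) and "Municipality-level IBP" for Brazil. The SAP does not expand IBP. It stands among the sociodemographic items and is read here as an area deprivation measure. Section 3.4 adds that in Brazil "data quality may vary geographically (typically data quality is better in the south of Brazil").

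**The concern.** The plan removes people who lack geography and then, in three of its four country-by-design models, names no geographic term. Records are lost without any confounding being controlled in return.

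Calendar-week dummies are national. They compare boosted with unboosted people in the same week across the whole country. If regions that boosted faster also had higher or lower incidence in that week, part of the regional difference is read as a booster effect. Uneven recording of outcomes, which section 3.4 allows for, would act in the same way, because the model sees recorded incidence.

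The RR for hospitalisation or death and the TND OR are both exposed. So is the waning trend: later post-booster categories draw on later weeks, and a regional pattern that changed over time could imitate a fall in protection or mask one.

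**Working it through.** **1. Which models name the terms**

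| Model | Geography named | Deprivation named | Listed as available |
|---|---|---|---|
| Scotland, cohort (5.1.3) | UR6, Health Board | SIMD | UR6, Health Board, SIMD |
| Brazil, cohort (5.1.3) | none | none | City (source blank), IBP |
| Scotland, TND (5.1.5) | none | none | UR6, Health Board, SIMD |
| Brazil, TND (5.1.5) | none | none | City (source blank), IBP |

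**2. What the omission could do**

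The SAP states no figure that depends on this point, so there is nothing to reproduce. The following is an illustration.

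*From the SAP (section 3.6):* Brazilian booster share 10M/49M = 20.4% (ChAdOx1) and 5M/28M = 17.9% (BNT162b2).

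*Assumed:* two equal regions A and B in one calendar week; booster shares cA and cB averaging 20%; incidence in A equal to R times that in B; the same true RR, t, in both.

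- Boosted rate = t(cA·R + cB)/(cA + cB)
- Unboosted rate = [(1−cA)R + (1−cB)]/[(1−cA) + (1−cB)]
- RR without region = boosted rate / unboosted rate

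With cA = 0.30, cB = 0.10 and t = 1:

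- R = 2: (0.60 + 0.10)/0.40 = 1.750; (1.40 + 0.90)/1.60 = 1.4375; ratio 1.22.
- R = 0.5: (0.15 + 0.10)/0.40 = 0.625; (0.35 + 0.90)/1.60 = 0.781; ratio 0.80.

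The factor does not depend on t. A true RR of 0.30 would appear as 0.365 or 0.24.

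| Booster share, A vs B | R = 0.33 | R = 0.5 | R = 1 | R = 2 | R = 3 |
|---|---|---|---|---|---|
| 20% vs 20% | 1.00 | 1.00 | 1.00 | 1.00 | 1.00 |
| 25% vs 15% | 0.85 | 0.90 | 1.00 | 1.11 | 1.16 |
| 30% vs 10% | 0.70 | 0.80 | 1.00 | 1.22 | 1.33 |

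**3. The TND**

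Here the regional factor is test positivity. Assume equal numbers tested in each region, shares 30% and 10%, positivity 30% in A and 15% in B, and a true OR of 1.00:

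- Boosted positive: 0.30×0.30 + 0.10×0.15 = 0.105
- Boosted negative: 0.30×0.70 + 0.10×0.85 = 0.295
- Unboosted positive: 0.70×0.30 + 0.90×0.15 = 0.345
- Unboosted negative: 0.70×0.70 + 0.90×0.85 = 1.255
- OR = (0.105×1.255)/(0.295×0.345) = 1.29 (1.295 before rounding, about 1.30)

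With positivity reversed, the OR is (0.075×1.225)/(0.325×0.375) = 0.75. With shares of 25% and 15% the two values are 1.14 and 0.87.

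Comparing within region returns the true value in every case, by construction. The distortion is nil if either booster share or incidence (positivity) is the same across regions within the week.

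**The case against.** The strongest reply is that the gap is one of drafting. The opening sentence of 5.1.3 names both factors before any country split, the lists are worded as anticipated, and the cohort model refers back to that section as a whole. This has some force for the Brazilian cohort: it may be an incomplete list rather than a decision to exclude geography. But considering a term does not commit to it, and the more specific list leaves it out. The TND list is stated on its own, so the omission is firmer there.

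The second reply points to other safeguards. Stratifying by the month of second dose may remove some regional difference in roll-out, but it does not equalise booster pace or incidence between regions. The inverse propensity weight covers the cohort only and its covariates are not listed. Negative-control outcomes are only to be considered, and they would show a problem rather than remove it.

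Four stronger readings are tempting and are not supported:

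- *That the estimates are biased, or that the bias changes sign as waves move.* The SAP gives no regional coverage, incidence or positivity, and says only that data quality may vary.
- *That the SAP calls deprivation essential.* Section 3.5 lists only sex, age and geography. Socioeconomic position is a confounder to be considered.
- *That race/ethnicity is not held in Scotland, so the Scottish TND model cannot be fitted.* It is absent from Table 1, but so is household size, which is in the Scottish adjustment set, and section 4.1 describes the tables as groupings of variables. The two places need reconciling; absence from the table proves nothing.
- *That the illustration shows false waning.* It covers one week and one boosted category. It shows how such an effect could arise, not that it does.

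**Conclusion.** The concern holds as a gap in specification. Followed as written, the Brazilian cohort model and the TND models in both countries leave geography and deprivation uncontrolled, contrary to the SAP's own confounder statement and, for geography, to its status as an essential covariate. Nothing else in the plan commits to closing the gap.

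The size is unknown. With average booster share near the SAP's figures and moderate regional contrasts (25% against 15%), the RR multiplier runs from 0.85 to 1.16 for incidence ratios of 0.33 to 3. With 30% against 10% it runs from 0.70 to 1.33. The regional shares, incidence ratios and positivity values are all assumptions. With populations this large, sampling error may be small beside errors of this order, and confidence intervals would not reveal them.

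**What to change.** - **Brazil, cohort and TND:** add a region term (state or another grouping of City) and municipality-level IBP. Define IBP and give the source of City in Table 2.
- **Scotland, TND:** add Health Board, SIMD and UR6, in line with the Scottish list in 5.1.3.
- **Both:** include a region-by-calendar-week term where event counts allow, at least as a sensitivity analysis. A region main effect alone does not capture epidemic timing that differs between regions.
- **Propensity score:** list its covariates and include the same variables.
- **Race/ethnicity:** reconcile the TND list with Table 1 for Scotland, either by stating the source or by giving each country its own list.

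The cost is SAP wording and more parameters. Those parameters are not free: the cohort models use all events plus 100 sampled individuals per event (10 for positive tests) within second-dose-month strata, and the TND uses tests rather than the whole population. Fine geography crossed with week could be sparse, above all for deaths, so a coarse region should be used there.
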